### Study population

The study population consists of pregnant women aged between 15 and 49 years in their second trimester (gestation period between 13 and28 weeks). Pregnancy status was confirmed by a validated pregnancy test report. The gestational age will be determined based on first date of last menstrual period by asking with the participant. The expected date of delivery (EDD) based on gestational age will be confirmed through physical examination of pregnant women by nursing staff. Women were excluded if they had the following characteristics: (a) those not planning to stay at the study site during pregnancy and postpartum, (b) any physical and mental disability (which can adversely influence the study results), (c) women who have miscarriage or still birth during recruitment process, and (d) woman who are not willing (to give consent) to participate in the study.

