### Study design

This is a two-parallel arms **cluster RCT** in rural community settings, provided participants are eligible for the study. Participants are recruited from 52 study areas by research assistants with the help of FCHVs. Then participants are then randomly assigned into intervention group and control arms based on clusters with approximately equal number of participations in each group.

Baseline information is collected after allocation of the clusters in two groups. At the same time, one-day extensive reinforcement training to the FCHVs in the intervention arm is conducted. Intervention group will receive text messages in their mobile phones. The principal investigator is responsible for sending text messages to the participants once they are recruited in the study and this process will continue until the fifth-month after childbirth. There will be three assessments during follow-up period and the data will be collected during these assessment periods: between 38 and 39 weeks of gestation, during delivery, and at 7 months after child birth. During the follow-up period, monitoring and supervision of FCHVs in the intervention arm will also be done to assess their performance. Additionally, assessment of child will be carried out at birth and 7 months after birth [Fig. 1].

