### Identification and recruitment of participants

All households with pregnant women in 52 clusters have been identified and screened applying inclusion and exclusion criteria. The identification of pregnant women has been made with the help of FCHVs’ antenatal registers. Pregnant women from each household in have been registered by FCHVs in their respective ward. All pregnant women with gestational period between 13 to 28 weeks are included in the study. Each household is coded and marked in the outside wall with a visible unique serial number to track participants during follow-up period.

The baseline information of these pregnant women was collected between July and September 2015. Selection of participants has been done by trained female research assistants (FRA), who are fluent in both Nepali and Maithili languages. Written informed consent have been taken from each participant who are willing to participate in the study. Participants are informed about the purpose of the study, advantages and any potential harms arising from a study. Head of the family, usually husband or close relatives of the relevant participants, were also informed about the study. For any adverse event or inquiry by the participants will be entertained or clarified.

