### Outcome measures

#### Primary and secondary outcomes of the study include;

Primary OutcomesUtilization of Skilled Birth Attendant (SBA) by pregnant women during delivery.Consumption of diversified diet by women during pregnancy and postpartum.

Secondary OutcomesFour ANC visits by pregnant womanDelivery of baby in a birthing centre (health care facility)PNC visits by mother and childWeight gain, haemoglobin changes and increase in uterine height of woman during pregnancyChanges in child feeding practices among mothers, andPerformance of FCHVs

Details of outcome measures are given in Additional file 5.

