### Data collection plan

The structured questionnaire has been piloted using responses from 20 households in the adjacent district. Necessary feedback is received and the amendment has been made in the final questionnaire before baseline data collection. Data will be collected by research assistants who are trained in the tools and techniques of data collection. Anthropometric assessment will be taken by six Female Research Assistants (FRAs) (one FRA per VDC).All measurements will be made three times and the median value will be recorded for analysis. The collection of information on pregnancy, outcomes and its determinants will be made longitudinally at different stages. The methods will employ structured interviews, FGD and anthropometric assessment.

Data will be collected at four chronological points. Baseline information on demographic characteristics, obstetric history, anthropometry, biochemical test, dietary survey and current practices on services utilization will be taken on 4–6 month prior to intervention. The reminders will be the follow-up period as described below;Assessment of pregnant women (services utilization, dietary survey, anthropometry and biochemical test) in the 9th month during intervention (Follow up- I).Data on birth weight will be taken by FRAs preferably within the first hour of the birth (Follow up II).Assessment of mother and child (services utilization, dietary survey and anthropometry including maternal and child morbidity) and satisfaction of the participants at the7th month after intervention (Follow up III).

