### Data management and analysis plan

Data entry will be performed in EpiData software version 3.1 and then it will be transferred to STATA software (Version 13.0) where all statistical analyses will be performed. The logistic regression model will be used to assess primary and secondary outcomes of the intervention. The independent t-test will be used to compare mean of different variables between the intervention and control groups. Chi-square test will be used to investigate the association between categorical variables in intervention and control groups. Within group analysis will also be done for outcomes whether it is attributed to either text message or capacity building or both.

For the repeated anthropometric measurement, biochemical test and dietary measures, we will use generalized estimating equation (GEE) and mixed model analysis to evaluate the effects of the intervention. The analysis will adjust for potential confounders for changes in weight gain and haemoglobin including baseline socio-demographic characteristics. We will also evaluate the possible interactions between the intervention indicators and participant attributes to assess the effect of intervention. Data will be analysed by ‘intention-to-treat’ principle.

Multiple imputations will be performed to account for missing data. Results will be expressed as odds ratios (ORs) with 95% confidence intervals for primary and secondary binary outcomes. Exploratory analysis will also be carried out on participant’s sub-groups to address heterogeneity. All test will be two-tailed and *p*-value will be set at < 0.05 for statistical significance.

All the FGDs will be recorded in a voice recorder. A coding framework will be prepared based on FGDs guideline. Transcription of data will be done in Nepali (National language), and then will be translated to English. Two researchers will be involved separately for coding based on pre-identified theme in the evaluation framework. Coding will be compared for consistency. The analysis will be done manually and no other software will be used for qualitative data analysis.

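### Weight gain, haemoglobin change and uterine-height increase are measured over 10 to 26 weeks depending on entry date, and the stated analysis does not name gestational age at baseline

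*Protocol article*

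**What the plan says.** The Study population section admits women "in their second trimester (gestation period between 13 and28 weeks", and the section on identification and recruitment agrees: "All pregnant women with gestational period between 13 to 28 weeks are included in the study". The Data collection plan words the timing of the baseline measurements differently: "anthropometry, biochemical test, dietary survey and current practices on services utilization will be taken on 4–6 month prior to intervention". Follow-up assessments are set in the Study design section "between 38 and 39 weeks of gestation, during delivery, and at 7 months after child birth". The Data collection plan places the first of them "in the 9th month during intervention (Follow up- I", which is compatible with 38 to 39 weeks.

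The Outcome measures section lists weight gain, haemoglobin change and uterine-height increase together as one secondary item, and adds: "Details of outcome measures are given in Additional file 5". That file is not part of the article.

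The Data management and analysis plan proposes independent t-tests for comparing means. It proposes GEE and mixed models for the repeated anthropometric, biochemical and dietary measures, without giving a time scale. On adjustment it says: "The analysis will adjust for potential confounders for changes in weight gain and haemoglobin including baseline socio-demographic characteristics". Uterine height does not appear in that sentence. Gestational age is obtained for each woman from the date of her last menstrual period (Study population).

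**The concern.** The start of the observation period varies by 15 weeks while its end is nearly fixed. A woman enrolled at 13 weeks has far longer to gain weight and uterine height than one enrolled at 28 weeks, whichever arm she is in. A t-test on the change treats both as the same measurement. So does a repeated-measures model that codes time as visit number. Socio-demographic covariates cannot stand in for weeks of observation.

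Two things are at stake. The first is precision: variation from entry date enters the error term although a recorded baseline variable could remove it. The second is comparability of the arms. The matching criteria (number of pregnant women, ethnic composition and use of skilled birth attendants) do not include gestation. Baseline is collected after the clusters are allocated, researchers and participants are not blinded, and women are identified through the volunteers' registers while the intervention volunteers are being trained. A difference between arms in baseline timing is therefore possible, and an unadjusted comparison would carry it into the result.

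**Working it through.** **The plan's own figures.** The article gives no sample size or variance for these three outcomes. Its calculation concerns skilled birth attendance and reproduces: (1.96 + 0.8416)² × (0.12×0.88 + 0.32×0.68) / 0.20² = 63.4, rounded up to 64; 64 × 2.29 = 146.6, so 147; 147 × 1.2 = 176.4, so 177 per arm. It is used below only for the number per arm.

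**Interval.** Shortest 38 − 28 = 10 weeks; longest 39 − 13 = 26 weeks; ratio 2.6.

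**Spread of entry week.** Assuming uniform entry over 13–28 weeks, SD = 15/√12 = 4.33 weeks.

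**Share of change-score variance due to entry week**, with linear growth at rate r and residual SD s: (r × 4.33)² / [(r × 4.33)² + s²]. The rates and residual SDs are assumptions, not figures from the article.

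| Outcome | r per week | s | Share |
|---|---|---|---|
| Weight gain, low | 0.2 kg | 4 kg | 0.75/16.75 = 4% |
| Weight gain, middle | 0.4 kg | 3 kg | 3/12 = 25% |
| Weight gain, high | 0.5 kg | 2 kg | 4.69/8.69 = 54% |
| Uterine height, low | 0.8 cm | 3 cm | 12/21 = 57% |
| Uterine height, high | 1.0 cm | 1.5 cm | 18.75/21 = 89% |

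For weight gain the share passes one half only in the extreme case shown. For haemoglobin the article supplies nothing from which to compute it.

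**Chance imbalance.** The standard error of the difference in mean entry week is 4.33 × √(2/177) = 0.46, so the 95% range is ±1.96 × 0.46 = ±0.9 week. If the design effect of 2.29 also applied to entry week (assumption), it is 0.9 × √2.29, about ±1.4 weeks. At 0.2–0.5 kg per week this is 0.9 × 0.2 ≈ 0.2 kg up to 1.37 × 0.5 ≈ 0.7 kg of weight gain. At 0.8–1.0 cm per week it is about 0.7 to 1.4 cm of uterine height.

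**Type I error.** 4,000 null trials were simulated with 26 clusters of 7 women per arm, uniform entry unrelated to arm, 0.4 kg per week and a residual SD of 3 kg. There was no matching and no added between-cluster variation. An unadjusted comparison of cluster means rejected in 4.5% of trials against a nominal 5%. Random entry timing alone does not inflate false positives.

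**Baseline window.** Read as calendar months of pregnancy, the sixth month ends at 6 × 30.44 / 7 = 26.1 weeks. Entry up to 28 weeks therefore reaches into the seventh month, about two weeks beyond the wording in the Data collection plan.

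**The case against.** The strongest reply is that the adjustment sentence is open-ended. It speaks of potential confounders and gives socio-demographic variables as an example, so gestational age is unnamed rather than ruled out. A condensed article may leave the covariate list to an analysis plan, the unseen additional file may define the outcomes per week, and gestational age could be the time scale of the mixed model. All of this stands: nobody can say from the article that gestational age was excluded. What remains is that the analysis the article does describe includes a t-test that cannot use entry week, and an adjustment that leaves out uterine height, the outcome most tied to gestation.

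A reader might infer that these outcomes largely measure when a woman enrolled. That fits uterine height under the assumed values. It is too strong for weight gain, and for haemoglobin the documents give no basis for it.

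A reader might also infer that any imbalance in entry week becomes a false treatment effect. Under randomisation with timing unrelated to arm, the imbalance is chance and the standard error carries it. Complete enumeration of eligible women and a baseline confined to July–September 2015 also limit arm-specific timing. They do not exclude it, since baseline still follows unblinded allocation.

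Finally, the mismatch in the baseline window is small, and read literally the month wording would narrow the interval.

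**Conclusion.** The point holds as a modest, cheap improvement to the analysis of three secondary outcomes. The 10-to-26-week interval follows directly from the stated visit schedule. Its cost is mainly precision: slight to substantial for weight gain, large for uterine height, unknown for haemoglobin. These sizes rest on uniform entry, linear growth and the assumed rates and residual SDs. Systematic bias is a possibility that depends on entry timing differing between arms; the article does not show that it did. The sample size and both primary outcomes are untouched.

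**What to change.** For weight, haemoglobin and uterine height alike, take the treatment effect from the GEE or mixed model already planned, not from the unadjusted t-test, and do one of the following:

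- include gestational age at baseline as a covariate; if both visits are modelled as outcomes, it must interact with visit, because a main effect alone shifts both visits equally and does not absorb the difference in change; or
- use gestational age as the model's time scale.

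Adjusting for gestational age at follow-up is not needed, because that visit is fixed at 38 to 39 weeks. Per-week reporting is optional. Tabulating gestational age at baseline by arm would show whether timing differed.

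Reconcile the month-based baseline wording in the Data collection plan with the weeks given in the Study population and recruitment sections.

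The cost is wording and a model re-run; no new data are needed, since gestational age is already recorded. The article states that the trial is completed, so unless an earlier analysis plan names this covariate, the adjusted analysis should be reported as a later addition and not as prespecified.

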**Method/design:**

MATRI-SUMAN is a 12-month cluster randomized controlled trial (RCT). The trial involves pregnant women from 52 clusters of six village development committees (VDCs) covering 66,000 populations of Dhanusha district of Nepal. In the intervention clusters, Female Community Health Volunteers (FCHVs) will receive capacity development skills through reinforcement training, supervision and monitoring skills for the promotion of health seeking behaviour among pregnant women and study participants will receive periodic promotional text messaging service about MCH components through mobile phones. A sample of 354with equal numbers in each study arm is estimated using power calculation formula. The primary outcomes of this study are the rate of utilization of skilled birth attendants and consumption of a specified diversified meal. The secondary outcomes are: four antenatal (ANC) visits, weight gain of women during pregnancy, delivery of a baby at the health facility, postnatal care (PNC) visits, positive changes in child feeding practices among mothers, performance of FCHVs in MCH service utilization.

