### Sample size estimation

The estimation of sample size was done considering the study design as two-parallel arm cluster RCT [26]. We assumed that 12% of the child births have been attended by a skilled birth attendant (SBA) at baseline in both arms and this rate will increase to 32% post- intervention in the intervention arm. 20% as the minimum difference between the two groups we would like to see after intervention with 0.80 power and 0.05 level of significance, and to account for intra-cluster correlation by taking the design effect of 2.29 for delivery attended by SBA, an adjusted sample size of 147 pregnant women in each arm is required for the study [4, 24]. With allowable 20% potential attrition, the final sample size is 177 for each arm. Thus, 354 pregnant women are estimated to be included in a trial. This number would be sufficient to detect a change in the effect sizes over a follow-up period in the intervention group as compared to control group. The study area consisted of 67,625populations (male/female ratio = 100:94) and the reported birth rate are 25.5 per 1000 per year [4], which gives an estimated 1724 expected pregnant women. Since, this study will consider the pregnant women in their second trimester, around 431 (=1724 × 0. 25) pregnant woman would be available at any point of time during a year, which is sufficient number for our study.

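### Two unranked primary outcomes are each tested at 0.05 with no success rule, and the sample size supports only skilled birth attendant use

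*Protocol article*

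**What the plan says.** The abstract puts two outcomes on an equal footing: "The primary outcomes of this study are the rate of utilization of skilled birth attendants and consumption of a specified diversified meal". The outcome list in Methods does the same and words the second as "Consumption of diversified diet by women during pregnancy and postpartum". Neither place ranks them or gives a rule for declaring success.

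The section Data management and analysis plan sets one standard for all comparisons: "All test will be two-tailed", and the p-value threshold "will be set at < 0.05 for statistical significance". It assigns logistic regression to the primary and secondary outcomes. For repeated measurements, among them the "dietary measures, we will use generalized estimating equation (GEE) and mixed model analysis to evaluate the effects of the intervention".

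The section Sample size estimation works only with SBA use: 12% against 32%, power 0.80, alpha 0.05, and a design effect of 2.29 given for SBA delivery. It arrives at 147 evaluable and 177 recruited women per arm, then adds a general assurance: "This number would be sufficient to detect a change in the effect sizes over a follow-up period in the intervention group".

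The last follow-up, which supplies the postpartum diet data, is dated in two ways. Study design lists assessments "during delivery, and at 7 months after child birth". Data collection plan places the visit in the 7th "month after intervention (Follow up III").

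**The concern.** With two primary outcomes, a plan has to say what counts as a positive trial. If either outcome suffices, testing each at 0.05 gives the trial more than a 5% chance of a false primary claim. If both are required, the type I error is controlled, but the power of the trial is the power to win on both, and one of the two was never sized. The article does not choose, so a reader of the results could not tell which of these two trials was run.

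The sufficiency sentence adds to the problem. It reads as cover for the trial's outcomes in general, while every input behind it belongs to SBA use.

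**Working it through.** **1. The article's own figure.** Inputs from Sample size estimation: p1 = 0.12, p2 = 0.32, two-sided alpha 0.05 (z = 1.960), power 0.80 (z = 0.842), design effect 2.29.

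- Variance sum: 0.12 × 0.88 + 0.32 × 0.68 = 0.1056 + 0.2176 = 0.3232.
- n = (1.960 + 0.842)² × 0.3232 / 0.20² = 63.4, rounded up to 64 per arm.
- 64 × 2.29 = 146.6, rounded up to 147.
- 147 × 1.2 = 176.4, rounded up to 177.

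Both stated figures reproduce with the unpooled formula, at the full 0.05, for SBA use alone.

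**2. Error rate if either outcome can carry the claim** (no effect on either; both tests two-sided at 0.05).

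| Correlation of the two test statistics | Chance of at least one p < 0.05 |
|---|---|
| 0 | 1 − 0.95² = 9.75% |
| 0.5 | 9.1% |
| 0.8 | 7.8% |
| 0.9 | 7.0% |
| Upper bound, any dependence | 0.05 + 0.05 = 10% |

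The correlated rows are 1 − P(|Z1| < 1.96 and |Z2| < 1.96) for a bivariate normal pair. The documents give no correlation, so the table shows a range.

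**3. Power if both must succeed.** Joint power cannot exceed the smaller of the two powers. Diet power cannot be computed from the article. For illustration only, assume a binary diet outcome, 147 evaluable women per arm, the SBA design effect carried over, a 20-point difference and a pooled-variance test:

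| Assumed control rate for diet | Power for 20 points | Smallest difference with 80% power |
|---|---|---|
| 10% | 82% | 19.6 points |
| 20% | 70% | 22.8 points |
| 30% | 64% | 24.2 points |
| 40% | 62% | 24.5 points |
| 50% | 64% | 23.8 points |

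The same pooled formula gives SBA use 78.8%. If the two tests were independent, the power to win on both would run from 0.788 × 0.623 = 49% to 0.788 × 0.816 = 64%.

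**4. Cost of the two usual remedies for SBA use.** The effective size is 147 / 2.29 = 64.19 per arm, the standard error is √(0.3232 / 64.19) = 0.0710, and 0.20 / 0.0710 = 2.819.

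- Fixed sequence, SBA first at 0.05: Φ(2.819 − 1.960) = 80.5%, unchanged.
- Bonferroni at 0.025: Φ(2.819 − 2.241) = 71.8%. Restoring 80% takes 77 × 2.29, or 177 evaluable per arm, and 177 × 1.2, or 213 recruited by the article's own inflation, against 177 recruited as stated.

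**5. Date of Follow-up III.** Study design counts from childbirth. Data collection plan counts from the intervention, without saying from its start or its end. Messages run to the fifth month after birth, so counting from the end gives month 5 + 7 = 12 postpartum, against month 7.

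**The case against.** The strongest reply is that the inflation is conditional. Nowhere does the article say that one positive outcome is enough, and the hypothesis and the Discussion join service use and diet with an and. This stands as far as it goes: a reader might infer that the family-wise error definitely exceeds 5%, and the text does not establish that. It does not establish a both-must-succeed rule either, and under that rule the weakness moves to the unsized outcome.

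Four further inferences are tempting and should be resisted.

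- *The diet outcome is given two conflicting models.* A GEE or mixed model with a logit link is logistic regression for repeated data. The natural reading is logistic regression for SBA use, measured once, and a repeated-measures model for diet.
- *The error rate is 14.3%, from 1 − 0.95³.* This needs separate, independent diet tests in pregnancy and postpartum. No section plans them, and a repeated-measures model can give one test. Two measurement occasions are not two hypothesis tests.
- *The diet definition is missing, or a null diet result cannot be interpreted.* The article refers outcome details to Additional file 5, which is not shown. Confidence intervals are planned for binary outcomes, and they show which effects are excluded.
- *Follow-up III is off by five months.* That gap rests on reading the later wording as after the end of the intervention. Seven months after birth fits the stated 12-month trial better: recruitment at 13 to 28 weeks puts that visit about 10 to 13 months after entry. The two wordings differ and need reconciling, no more.

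An unseen analysis plan might also set a testing order. The uniform 0.05 threshold and the SBA-only sizing are nevertheless stated in this article.

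**Conclusion.** The point holds in a conditional form. There are two unranked primary outcomes, one two-sided 0.05 threshold and no success rule. If either outcome suffices, the family-wise error when neither is affected is up to 9.75% for independent tests, about 7.0% at a correlation of 0.9, and at most 10%. If both are required, the error rate is held at 5% and the power of the trial rests on an outcome with no stated assumptions. In both cases the general sufficiency sentence is supported for SBA use only. The diet powers above depend on assumed control rates and a borrowed design effect. They show that 80% cannot be taken for granted, not that diet is underpowered. The Follow-up III dates are a minor inconsistency that affects the postpartum part of the diet outcome. This should be corrected, but it does not invalidate the SBA analysis.

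**What to change.** State a fixed sequence: SBA use at two-sided 0.05, then diversified diet at two-sided 0.05 only if SBA use is significant. Making SBA use the single primary and diet the key secondary has the same effect. Either follows the article's own sizing and leaves SBA power at 80.5%, where a Bonferroni split would lower it to 71.8%.

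For diet, specify one treatment test from one repeated-measures model that accounts for clustering by ward and covers both the pregnancy and postpartum surveys. This keeps the listed outcome whole; naming only the antenatal visit as primary would drop half of it. Reword the sufficiency sentence so that it applies to SBA use only, and give Follow-up III one date in Study design and Data collection plan.

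The cost is mainly in wording, with two real downsides. Diet can be claimed only after SBA use succeeds. And because the section Trial status reports the trial as completed, a testing order introduced now cannot be presented as prespecified: it has to be disclosed as post hoc unless an earlier dated document contains it.
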